**Fig. 2 Fig2:**
[figure not shown]
Data collection timeline (SPIRIT figure). HFS, hand-foot syndrome; PRO, patient-reported outcome; Cox-2, cycloxygenase-2

#### Sample size {14}

We calculated the sample size for the study using the chi-square test. With 120 patients in each study arm, there will be at least 80% power to detect a difference in HFS rates at a two-sided 0.05 significance level, using a chi-square test. This assumes that the rate of grade 2 or higher HFS is 30% in the control arm and 15% in the experimental arm. Assuming approximately 10% attrition, we plan to recruit 264 patients.

#### Recruitment {15}

Recruitment will take place in the outpatient breast and gastrointestinal cancer clinics at [name] Institute Rotary Cancer Hospital, All India Institute of Medical Sciences, New Delhi, India. Since it is a large volume teaching hospital, we expect to recruit the planned number of patients in two years.

#### Assignment of interventions

##### Sequence generation {16a}

A permuted block, computer-generated (www.sealedenvelope.com), randomization sequence with variable block size, stratified by sex (male or female), and type of therapy (capecitabine monotherapy or combination therapy) will be used to allocate participants in a 1:1 ratio.

##### Concealment mechanism {16b}

Allocation concealment will be ensured by using opaque, sealed, and sequentially numbered envelopes. The numbering of the envelopes will be conducted in advance and will be opened only after writing the participant’s name on the envelope.

##### Implementation {16c}

The allocation sequence will be generated by a person who is not involved with enrolment or future data collection and analysis. Participants will be screened and randomized at the time of planning capecitabine-based chemotherapy regimens in the outpatient clinics.

##### Blinding {17a}

The trial is a double-blind study. To ensure blinding, the statistician will label the placebo and diclofenac tubes with unique alphanumeric codes (e.g. AA1B) that are generated by the computer with the random sequence. The tubes, the packets, and the labels will look exactly the same. The study investigators and the enrolled patients will not be aware of the contents of the tubes.

##### Procedure for unblinding {17b}

The blinding will be broken by the investigator only in case of a medical emergency, where knowledge of the study drug is critical for the management of the subject’s immediate treatment. The Institute Ethics Committee will be contacted in case of unblinding for a study participant.

### Data collection and management

#### Plans for assessment and collection of outcomes {18a}

Data will be collected by the research staff at every site visit using printed copies of case record forms that will be stored in a locked compartment at the study site. All study parameters are defined a priori in a data dictionary describing data collection.

#### Plans to promote participant retention and complete follow-up {18b}

Participants will be assessed every 3 weeks and will be contacted by telephone, in case they miss their clinic appointment with the treating oncologist.

#### Data management {19}

Data entry and coding will be done manually by the research staff for the study. Data will be kept secured and stored in password-protected folders with limited access to authorized individuals.

#### Confidentiality {27}

The identifying information of study participants will be removed, wherever possible. Each study participant will be allotted a study identification number and the case record forms will contain only the de-identified data. Consent forms containing the identifying data of patients will be kept in locked compartments at the study site that can exclusively be accessed by authorized personnel.

#### Plans for collection, laboratory evaluation and storage of biological specimens for genetic or molecular analysis in this trial/future use {33}

Blood samples will be collected at pre-defined two time points, as mentioned in Fig. 2. The samples will be stored as serum and extracted DNA at − 80 °C to assess COX-2 levels and DPD polymorphism, respectively. The left-over samples will be stored at − 80 °C for future use.

## Statistical methods

### Statistical methods for primary and secondary outcomes {20a}

The primary end-point (≥ grade 2 HFS) will be compared between the two study groups by the chi-squared test, and the risk difference presented with 95% confidence intervals. The significance level will be kept at 0.05 (two-sided).

The primary analysis will be adjusted for the stratification factors used in randomization (sex and type of therapy).

Patient demographic, clinical and treatment characteristics, and other study outcomes will be described (within randomized groups and overall) using mean, standard deviation and range or median, interquartile range, and range for continuous variables and frequencies and percentages for categorical variables. Continuous variables will be checked for normality and log transformation will be conducted, where necessary. Study outcomes will be compared between the groups using standard statistical methods—two sample *t*-tests or appropriate non-parametric tests for continuous outcomes, chi-square tests for categorical outcomes, and the log-rank test for time to event outcomes. Effect sizes and 95% confidence intervals will be presented where possible. The analysis will be performed using the Stata statistical software (StataCorp. 2013. Release 13. College Station, TX) and R version 4.1.1 (R Foundation for Statistical Computing, Vienna, Austria).

### Methods for additional analyses {20b}

Subgroup analyses will be performed for sex (male vs female) and type of therapy (monotherapy vs combination therapy). Exploratory analyses for predictors of outcomes, and adjusted analyses, will use regression models including proportional hazards, logistic, and linear regression. The baseline serum Cox-2 levels will be compared with the follow-up sample by paired t-test.

### Interim analyses {21b}

No interim analysis is planned as there are minimal safety concerns with the topical application of diclofenac.

### Methods in analysis to handle protocol non-adherence and any statistical methods to handle missing data {20c}

All analyses will include all patients who were randomized and conducted using the intention-to-treat principle whereby patients are analysed according to randomized treatment regardless of treatment received. Self-reported adherence diaries will be checked and adherence will be encouraged, wherever necessary. Missing data will be checked for randomness using Little’s test [19].

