### Objectives {7}

We hypothesize that the application of 1% topical diclofenac will decrease the incidence of capecitabine-induced HFS (grade 2 or higher) by 15%, when compared with placebo.

The primary objective of this study is as follows:

1. To compare the effect of topical diclofenac with placebo in preventing HFS (incidence of NCI CTCAEv5.0 grade 2 or higher HFS)

The secondary objective is to compare the effect of topical diclofenac with placebo on the following:Preventing all grades of HFS (incidence of NCI CTCv5.0 all grade HFS)Time to develop HFS (from the start of capecitabine)Patient-reported outcomes (PROs) (HF-HRQoL Questionnaire)Adherence with the application (self-reported)Capecitabine dose changes (number of patients with dose modifications due to HFS)Safety profile (NCICTCv5.0 all grade HFS)

The tertiary correlate objectives are as follows:

1. To correlate the occurrence and severity of HFS with COX-2 levels (serum COX-2 levels)

2. To correlate the occurrence and severity of HFS with genetic polymorphism of dihydropyrimidine dehydrogenase (DPD) enzyme

The primary assessment time for the primary outcome is 4 cycles of capecitabine-based therapy, which amounts to 12 weeks.

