### Outcomes {12}

The primary outcome of the study is the proportion of patients who develop grade 2 or higher HFS, as defined by the NCI CTCAE version 5.0 (Table 1).

**Table 1 Tab1:** NCI CTCAEv5.0 grading for HFS/palmar plantar erythrodysesthesia

Grade	Description
**Grade 0**	No symptoms
**Grade 1**	Minimal skin changes or dermatitis (e.g. erythema, oedema, or hyperkeratosis) without pain
**Grade 2**	Skin changes (e.g. peeling, blisters, bleeding, oedema, or hyperkeratosis) with pain; limiting instrumental ADL
**Grade 3**	Severe skin changes (e.g. peeling, blisters, bleeding, oedema, or hyperkeratosis) with pain; limiting self-care ADL

*ADL* activities of daily living

The primary, secondary and tertiary outcomes of the study are described in Table 2.

**Table 2 Tab2:** Primary, secondary and tertiary outcomes of the study

Outcome	Description
Primary outcomes	Grade 2 or higher HFS (proportion)
Secondary	All grades of HFS (proportion) Time to develop HFS (days) Patient-reported outcomes using HFS 14 questionnaire Adherence with topical application HFS related dose changes and delays in capecitabine Adverse events (NCI CTCAE version 5.0)
Tertiary	COX-2 levels

*HFS* hand-foot syndrome, *NCI* National Cancer Institute, *CTCAE* Common Terminology Criteria for Adverse Events, *COX-2* cycloxygenase-2

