#### Composition of the data monitoring committee, its role, and reporting structure {21a}

The study does not have a data monitoring committee as there are minimal safety concerns with the use of topical diclofenac. However, serious adverse events, if any, will be reviewed by the trial steering committee and reported to the Institute Ethics Sub Committee for Monitoring of Adverse Events in Clinical Trials at the site.

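### The all-randomised, as-assigned rule is worded to cover adverse events as well as efficacy, which slightly shrinks any gel-related difference in harms (low severity)

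*Protocol article*

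**What the plan says.** The section on non-adherence and missing data {20c} in the protocol article states: "All analyses will include all patients who were randomized and conducted using the intention-to-treat principle". It adds that "patients are analysed according to randomized treatment regardless of treatment received". No outcome is excepted.

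Three other sections bring harms under that rule:

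- **Outcomes {12}, Table 2** lists "Adverse events (NCI CTCAE version 5.0") among the secondary outcomes.
- **Objectives {7}** puts safety among the items on which diclofenac is to be compared with placebo: "Safety profile (NCICTCv5.0 all grade HFS"). The bracket there names only the hand-foot syndrome grading, but Table 2 shows that adverse events are meant as an outcome in their own right.
- **Statistical methods {20a}** says that study outcomes are compared between the groups, with "chi-square tests for categorical outcomes".

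The article names no safety set and no as-treated set.

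**The concern.** Keeping every randomised patient in the assigned arm is the right primary approach for efficacy in a superiority trial, because dilution there works against the claim being made. For harms the direction reverses. A patient who never applies gel cannot have a reaction to it, so including that patient moves the arms together and makes the gel look safer. If a patient received the wrong coded pack, events would also be counted against the gel that was not used.

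The design allows for never-starters. Randomisation takes place while capecitabine is still being planned (Implementation {16c}), and the eligibility criteria allow study treatment to start up to 14 days after randomisation. A patient can drop out of treatment in that gap.

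The comparison has some weight because the final table is the only between-arm look at harms that the article plans. It states "No interim analysis is planned as there are minimal safety concerns with the topical application of diclofenac" and "The study does not have a data monitoring committee as there are minimal safety concerns with the use of topical diclofenac". Serious events go to the steering committee and the ethics sub-committee, but no comparison by arm is described for that review.

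**Working it through.** **Figures in the plan.** The article gives no adverse-event rate and no expected share of never-starters, so there is no stated safety figure to reproduce. The sample size section supplies only the arm size: 240 x 1.10 = 264 recruited, and 264 / 2 = 132 per arm. The sizing itself (30% vs 15%, 120 per arm) reproduces to rounding, with 79.8% power, and is unaffected by this point.

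**Model.** Let p0 be the background adverse-event rate on capecitabine, p1 the rate in patients who use diclofenac gel, and f the share who never apply gel. Assume that never-appliers have the background rate and that placebo gel adds no events.

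- Diclofenac arm, all randomised: (1 - f) x p1 + f x p0
- Placebo arm, all randomised: p0, unchanged
- Difference: (1 - f) x p1 + f x p0 - p0 = (1 - f) x (p1 - p0)

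The difference attributable to the gel therefore shrinks by exactly the share f, always towards zero. The placebo percentage does not move.

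**Numbers.** The rates are assumptions: p1 = 15%, p0 = 5%, a true difference of 10.0 points. Power is for a two-sided 0.05 chi-square test, with 132 per arm (all randomised) or 132 x (1 - f) per arm (exposed only).

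| f (assumed) | Difference, all randomised | Power, all randomised | Power, exposed only |
|---|---|---|---|
| 2% | 0.98 x 10.0 = 9.8 | 76.3% | 76.8% |
| 5% | 0.95 x 10.0 = 9.5 | 74.2% | 75.5% |
| 10% | 0.90 x 10.0 = 9.0 | 70.5% | 73.2% |
| 20% | 0.80 x 10.0 = 8.0 | 62.3% | 68.0% |

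With 10% vs 2% instead, the difference of 8.0 points becomes 7.8, 7.6, 7.2 and 6.4.

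**In events.** One event in 132 patients is 1 / 132 = 0.76 points. For the 10.0-point case, the shift is 0.2 x 1.32 = 0.3 events at f = 2%, 0.5 x 1.32 = 0.7 at 5% and 1.0 x 1.32 = 1.3 at 10%.

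**Sensitivity to the model.** Suppose never-appliers had no recorded adverse events at all, for instance because they never started capecitabine either, and f is the same in both arms. At f = 10%, the rates would be 0.90 x 15% = 13.5% and 0.90 x 5% = 4.5%. The difference is again 9.0 points. Both models give the same difference; only the second lowers both percentages.

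**The case against.** **This belongs to the analysis plan.** A condensed article may leave the naming of a safety set to a document that is not shown. That would answer a complaint that the article is silent, but it is not silent. It states a rule for every analysis, and a plan that used an exposed set for harms would depart from that sentence as written.

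**An all-randomised harms table is defensible.** It keeps the randomised comparison, whereas an exposed set is defined by what happens after randomisation. This stands as a reason to keep the all-randomised table. It weighs less as a reason to use that table alone, because the trial is double-blind and a patient's failure to start gel should not depend on knowing the arm.

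**The effect is small.** This stands. At f = 5% or below, the illustrated shift is less than one event, and the power difference is 1.3 points or less.

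Some stronger readings are tempting, and the documents do not support them:

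- A reader might infer that every adverse-event percentage falls by the never-applied share. The patients are starting capecitabine, which has toxicities of its own, so a patient on capecitabine without gel still has background events. It is the difference attributable to the gel that shrinks.
- A reader might take the roughly 10% attrition in the sample size section as the never-applied share. That figure covers losses in general and says nothing about patients who never start gel.
- A reader might treat pack mix-ups as a material problem. Tubes are coded to the randomisation number, and nothing in the article suggests that errors would be frequent.
- A reader might see the lack of a data monitoring committee or interim look as making the bias worse. Neither affects the final safety denominator.

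**Conclusion.** The point holds as a wording fault of low severity. As written, the rule in {20c} sends the adverse-event comparison through an all-randomised, as-assigned analysis, and this multiplies any gel-attributable risk difference by (1 - f). The direction is certain under the stated assumptions: never-appliers carry the background rate, and placebo gel adds none. The size is not known, because the article gives neither f nor adverse-event rates. Over an assumed f of 2% to 10%, a true 10.0-point difference is reported as 9.8 down to 9.0, and power is 0.5 to 2.7 points below that of an exposed-only analysis.

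That is unlikely to change a safety conclusion, and the article gives no ground for saying that it would. The case for changing the text rests on the direction of the error and the very low cost of removing it. Efficacy inference is not affected.

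**What to change.** Limit the sentence in {20c} to efficacy outcomes and add a rule for harms along these lines:

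- Adverse events are analysed in all patients who applied study gel at least once, grouped by the gel actually received, as shown by the pack code.
- A patient who was dispensed a pack but whose use is unknown counts as exposed. This is needed because exposure is read from a self-completed diary and returned tubes, and a patient who withdraws before the first visit may return neither.
- The number never exposed is reported for each arm.
- The all-randomised adverse-event table is given as a supplement.

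The cost is a few lines of text. Diaries, tube returns and pack codes are already part of the trial, so nothing new has to be collected. The drawbacks are a slightly smaller safety denominator and a set defined after randomisation. Blinding and the supplementary table mitigate the second.

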### Oversight and monitoring

#### Composition of the coordinating centre and trial steering committee {5d}

The study will be coordinated by the principal investigator at the All India Institute of Medical Sciences, New Delhi. The trial steering committee will be formed by the investigators from the departments of Medical Oncology at the study site. Study coordination, monitoring, data acquisition and management, and statistical analysis will be performed by the principal investigator of the study.

#### Composition of the data monitoring committee, its role, and reporting structure {21a}

The study does not have a data monitoring committee as there are minimal safety concerns with the use of topical diclofenac. However, serious adverse events, if any, will be reviewed by the trial steering committee and reported to the Institute Ethics Sub Committee for Monitoring of Adverse Events in Clinical Trials at the site.

#### Adverse event reporting and harms {22}

Adverse events will be collected in accordance with the guidelines. Serious adverse reactions will be reported to the Institute Ethics Sub Committee for Monitoring of Adverse Events in Clinical Trials at the site.

#### Frequency and plans for auditing trial conduct {23}

After the start of the study, the trial steering committee will audit the consenting process, protocol adherence, and data collection, at six-monthly intervals. The data may be subject to audit or inspection by representatives of the Institute Ethics Committee.

#### Plans for communicating important protocol amendments to relevant parties {25}

Protocol amendments will be promptly reported to the Institute Ethics Committee and the Clinical Trials Registry of India.

#### Protocol amendments

No protocol amendment has been done till date.

#### Dissemination plans {31a}

The study will be published in a peer-reviewed journal with authorship consisting of the individual investigators and the group name ‘D-TORCH’ study investigators’. Full credit will be given to all collaborating investigators, and research staff involved in the conduct of the study. All authors will approve the manuscript prior to submission and also comply with the internationally agreed upon requirements. We will also present the results of the trial at one or more major scientific meetings. We will ensure that results are available to study participants.

#### Research ethics approval{24}

The study protocol was approved by the Institute Ethics Committee of All India Institute of Medical Sciences, New Delhi, on January 11, 2021 (IEC-1136/06.11.2020).

#### Authorship guidelines {31b}

The International Committee of Medical Journal Editors (ICMJE) guidelines will be followed for publishing the protocol and the final manuscript. No professional writers will be employed for drafting the manuscript.

#### Access to protocol, dataset, and statistical code {31c}

Full protocol, deidentified dataset, and statistical code will be provided as supplementary material to the final manuscript.

## Conclusions

The pathophysiology of HFS includes activation of COX-2, leading to an upregulation of the inflammatory cascade. Although systemic Cox-2 inhibitors are effective in preventing HFS, they are not used routinely because of the concerns regarding cardiotoxicity. No clinical trials have assessed the role of topical non-steroidal anti-inflammatory drugs (NSAIDs) in preventing HFS. The D-TORCH study is a randomized phase III, placebo-controlled, double-blind, parallel-group, superiority trial designed to assess the efficacy of 1% topical diclofenac in preventing capecitabine-associated HFS.

## Trial status

Recruitment of the first participant occurred on February 10, 2021, and 75 patients have been recruited by 25 August 2021. Although there was an impact on recruitment due to the second wave of COVID-19 pandemic in India, the study is progressing as expected, and it is anticipated that the last patient will be recruited by the end of September 2022, and follow-up will be completed by December 2022, thereby completing the study on time. No protocol amendments have been made to date.

## Data Availability

After the completion of the study, datasets will be made available as per the policy of the Institute Ethics Committee. There are no disclosures to be made that would restrict the availability of data.
